## Abstract

**Background:**

The preoperative period can be used to enhance a patient’s functional capacity with multimodal prehabilitation and consequently improve and fasten postoperative recovery. Especially, non-small cell lung cancer (NSCLC) surgical patients may benefit from this intervention, since the affected and resected organ is an essential part of the cardiorespiratory fitness. Drafting a prehabilitation programme is challenging, since many disciplines are involved, and time between diagnosis of NSCLC and surgery is limited. We designed a multimodal prehabilitation programme prior to NSCLC surgery and aimed to conduct a study to assess feasibility and indicative evidence of efficacy of this programme. Publication of this protocol may help other healthcare facilities to implement such a programme.

**Methods:**

The multimodal prehabilitation programme consists of an exercise programme, nutritional support, psychological support, smoking cessation, patient empowerment and respiratory optimisation. In two Dutch teaching hospitals, 40 adult patients with proven or suspected NSCLC will be included. In a non-randomised fashion, 20 patients follow the multimodal prehabilitation programme, and 20 will be assessed in the control group, according to patient preference. Assessments will take place at four time points: baseline, the week before surgery, 6 weeks postoperatively and 3 months postoperatively. Feasibility and indicative evidence of efficacy of the prehabilitation programme will be assessed as primary outcomes.

**Discussion:**

Since the time between diagnosis of NSCLC and surgery is limited, it is a challenge to implement a prehabilitation programme. This study will assess whether this is feasible, and evidence of efficacy can be found. The non-randomised fashion of the study might result in a selection and confounding bias. However, the control group may help putting the results of the prehabilitation group in perspective. By publishing this protocol, we aim to facilitate others to evaluate and implement a multimodal prehabilitation programme for surgical NSCLC patients.

**Trial registration:**

The current study is registered as NL8080 in the Netherlands Trial Register on the 10th of October 2019, https://www.trialregister.nl/trial/8080. Secondary identifiers: CCMO (Central Committee on Research Involving Human Subjects) number NL70578.015.19, reference number of the Medical Ethical Review Committee of Máxima MC W19.045.

## Background

Worldwide, lung cancer is the leading cause of cancer death and has the highest incidence amongst cancer types (Bray et al. 2018). The preferred curative treatment option for resectable non-small cell lung cancer (NSCLC) is anatomical resection combined with mediastinal lymph node dissection. However, surgery and postoperative complications contribute to significant morbidity. Major pulmonary complications negatively impact long-term outcomes, including a reduced disease-free survival (Wang et al. 2017). Furthermore, pulmonary complications affect patient-centred outcomes and healthcare costs (Templeton and Greenhalgh 2019).

In the past decades, the preoperative period has been used more and more to prepare patients for surgery by means of prehabilitation. These multimodal prehabilitation programmes aim to enhance functional capacity, prepare patients for treatment and consequently and improve outcome. The first official guidelines for enhanced recovery after lung surgery by the Enhanced Recovery After Surgery (ERAS®) Society and the European Society of Thoracic Surgeons (ESTS) strongly recommend prehabilitation for patients with borderline lung function or exercise capacity (Batchelor et al. 2019). Several systematic reviews and meta-analyses on the effect of various preoperative interventions prior to lung cancer surgery have recently been published, reporting a reduction in postoperative (pulmonary) complications and length of hospital stay (Cavalheri and Granger 2017; Kendall et al. 2018; Rosero et al. 2019; Steffens et al. 2018). In addition to these benefits, patients deemed unfit for surgery, based on their pulmonary function test and exercise test results, could potentially become a surgical candidate with prehabilitation (Mahendran and Naidu 2018).

To date, delaying surgery for patients with lung cancer to facilitate prehabilitation cannot be recommended, because cancer could potentially progress (Cavalheri and Granger 2017; Mahendran and Naidu 2018). The Dutch national guideline for the treatment of NSCLC states that 80% of patients should be operated within 2 weeks after completion of the diagnostic phase (National guideline non-small cell lung cancer n.d.). This is monitored by the Dutch Institute for Clinical Auditing (DICA) through the compulsory Dutch Lung Cancer Audit — Surgery (DLCAs), which records and benchmarks the percentage of operations performed within 3 weeks from the time of the multidisciplinary team meeting confirming diagnosis (Dutch Institute and for Clinical Auditing n.d.). The window of opportunity prior to surgery to optimise patients is therefore limited, yet meaningful improvements from such interventions have been demonstrated in a recently published randomised controlled trial with a multimodal prehabilitation programme in a home-based setting with a 2-week window before surgery (Liu et al. 2020).

The aim of this multicentre, non-randomised study is to evaluate feasibility and assess indicative evidence of efficacy of a supervised high-intensity multimodal prehabilitation programme for surgical NSCLC patients in the Dutch healthcare system. By publishing the protocol of our study, we aim to encourage colleagues to implement a similar programme in their own facilities more easily and possibly adjust it to use for other patient populations as well. Publication of this protocol enables us to describe the programme more detailed, than when reported simultaneously with the final results of our study. Besides, this publication will contribute to transparency in the conduction of studies.

## Methods

### Study design and setting

Our study is a non-randomised feasibility study, approved by the Medical Ethical Review Committee of Máxima MC (MMC) (reference number: W19.045) and the Institutional Review Board of the Albert Schweitzer Hospital (ASz). Patient recruitment commenced in January 2020 and was temporarily interrupted between March 2020 and June 2020 due to the coronavirus disease 2019 (COVID-19) pandemic. The two Dutch teaching hospitals have expertise regarding prehabilitation programmes for oncological surgery and enhanced recovery after thoracic surgery.

For this protocol, the reporting standards of the SPIRIT (Standard Protocol Items: Recommendations for Interventional Trials) checklist, adapted for pilot and feasibility studies, were used as guidance (Thabane and Lancaster 2019).

### Participants

All consecutive patients meeting the inclusion criteria will be asked to participate in the multimodal prehabilitation programme. Patients are deemed eligible when ≥ 18 years of age, with pathologically confirmed or suspected NSCLC and an indication for anatomical lung resection. Furthermore, a straightforward preoperative work-up is needed to ensure patients can enter the programme directly after diagnosis in order to use the window of opportunity between diagnosis and surgery as efficient as possible. Also, the ability to provide written informed consent is needed for inclusion. Eligible patients not willing to participate in the multimodal prehabilitation programme will be asked to participate in the control group. The control group may provide insight in the course of functional capacity perioperatively and will enable comparison with the prehabilitation group.

Exclusion criteria comprise a contra-indication for training, renal insufficiency (defined as estimated glomerular filtration rate (eGFR) < 60 ml/min/1.73 m^2^) or participation in other trials that may interfere. Referred patients from another hospital with the diagnostic phase already completed will be excluded, for logistical reasons, travel distance and the probability that these factors may affect feasibility of the programme. If a contra-indication for training will become apparent after signing informed consent and following baseline assessment, we intend to exclude the subject from participation for safety reasons. Furthermore, if the postoperative pathology results will not confirm the diagnosis NSCLC, the data of this patient will be included in the analysis; however, we intend to recruit an extra patient to finally include a total of 40 patients with confirmed NSCLC, per centre ten patients in the prehabilitation group and ten in the control group. All assessed patients will be logged.

The sample size of 40 participants for this feasibility study is based on a previously performed pilot study in colorectal cancer patients (Rooijen et al. 2019). This study was able to assess feasibility and indicative evidence of efficacy with a similar sample size. Patients will be selected and informed about the study during a visit to their treating pulmonologist in the outpatient clinic. Informed consent will be obtained by a member of the research team during a face-to-face consult in the outpatient clinic prior to baseline assessment. We intend to conduct the study and finish follow-up between January 2020 and January 2022. The SPIRIT-derived Fig. 1 displays an overview of the time points, assessments and recorded variables.

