### Assessments

Both groups will be assessed at baseline, the week before surgery, 6 weeks postoperatively and 3 months postoperatively.

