#### Exercise programme

The exercise programme consists of in-hospital, supervised training on three nonconsecutive days per week, for about 60 min, consisting of high-intensity interval training (HIIT) endurance training and strength exercises. Patients will be supervised by a physiotherapist, specialised in oncology and preferably train in peer groups if permitted by the periodicity of inclusion of subjects and existing COVID-19 measures. The intensity of the exercise programme will be individualised based on the baseline assessment and will be continuously evaluated by the physiotherapist during the programme.

The HIIT will be performed on a bicycle ergometer and consists of two series of eight repetitions of uninterrupted cycling. One repetition consists of 30 s of strain, set on 65% of the MSEC measured with the SRT, followed by 30 s of rest being 30% of the MSEC. Intensity of the HIIT will be monitored and adjusted, if necessary: if a patient scores ≤ 11 on the Borg scale (Achttien et al. 2011), the intensity will be increased by 5%; intensity will be decreased by 5% when the Borg score is ≥ 15 or when a patient will not be able to complete the eight repetitions.

The supervised strength exercises will be performed on fitness devices, and the intensity will be based on the 1-RM strength test calculation at baseline. The intensity will start with 65% of 1-RM in week 1, will increase to 70% in week 2 and if time allows 75% in week 3. Strength training will consist of two series of ten repetitions of the following exercises, targeting major muscle groups: lateral pull down, leg press, chest press and low row.

Finally, patients will be instructed by the physiotherapist to perform out-of-hospital exercises — like walking or cycling, according to patient preference — with low to moderate intensity, on the remaining 4 days of the week for at least 60 min per day.

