### Outcome measures

#### Primary outcomes

The main primary outcome of this study is feasibility of the prehabilitation programme. Feasibility is defined as ≥ 80% protocol adherence (per intervention) of at least 80% of the participants in the prehabilitation group. To determine feasibility, we will collect the following data: number of eligible patients, number of patients enrolled, number of drop outs, number of attended supervised training sessions (per patient), patient’s logging booklet (number of out-of-hospital low to moderate training, recorded intake of nutritional supplements) and activity monitor data. The second primary outcome is functional capacity. Functional capacity will be determined at baseline, the week prior to surgery and 6 weeks postoperatively. Change over time compared to baseline within and between groups will be determined.

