#### Secondary outcomes

The following secondary outcomes will be studied:Programme evaluation as a whole and per intervention (based on compliance, patient satisfaction and experience of the research team)Effect on clinical outcome: 30-day mortality, length of hospital stay, 30-day complication rate expressed as the comprehensive complication index (Slankamenac et al. 2013) and readmission rate. This will be compared to the control group and a historical Dutch cohort as recorded in the DLCAs (Dutch Institute and for Clinical Auditing n.d.).Cost-effectiveness of the prehabilitation programmeEfficacy of the programme on nutritional and mental health status, smoking cessation and quality of life compared to baseline and control groupCorrelation between VO2max estimated with the physical condition questionnaire (FitMax^©^) and as determined with the SRT and, if applicable, CPET

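### The exclusion for a contra-indication to training has no end date, so once the programme is running it may remove less fit patients from the prehabilitation group only

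*Protocol article*

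**What the plan says.** A contra-indication to training is a study-level exclusion criterion in the Participants section: "Exclusion criteria comprise a contra-indication for training, renal insufficiency". The section then covers late discovery: "If a contra-indication for training will become apparent after signing informed consent and following baseline assessment", the consequence is "we intend to exclude the subject from participation for safety reasons". It names no group and sets no limit on how late the finding may come. It does not say whether follow-up continues or whether data already collected are analysed. The sentence that follows deals with another problem found after enrolment, pathology that does not confirm NSCLC. There it expressly keeps the patient's data in the analysis and recruits an additional patient.

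Controls come from the same eligible pool: "Eligible patients not willing to participate in the multimodal prehabilitation programme will be asked to participate in the control group". Under Assessments, "Both groups will be assessed at baseline, the week before surgery, 6 weeks postoperatively and 3 months postoperatively". The Physical status section places the walk, steep ramp and strength tests at baseline, in the week before surgery and at 6 weeks. Between the first two of these, the prehabilitation group alone has "in-hospital, supervised training on three nonconsecutive days per week".

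The comparisons affected are the second primary outcome, functional capacity ("Change over time compared to baseline within and between groups will be determined"), and the clinical outcomes compared with controls, which include "30-day mortality, length of hospital stay, 30-day complication rate expressed as the comprehensive complication index".

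**The concern.** The stated reason is safety, and the hazard is training. That reason can support not training. It gives no evident ground for ending e-mailed questionnaires or the recording of surgical and 30-day outcomes. Yet the wording ends participation, and the contrast with the next sentence, where data are expressly kept, makes removal from the study the plain reading.

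A rule of this kind selects patients after enrolment. If it removes less fit patients from one group more often than from the other, functional capacity, complications and length of stay may look better in that group even if the programme has no effect. Outcomes that were never collected cannot be recovered at the analysis stage. The mixed model cannot use them, and the rule that scores missing data as not performed applies to feasibility only. For a patient whose contra-indication surfaces during training, those outcomes would also bear on the safety of the programme.

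**Working it through.** **No figure of the plan to reproduce.** The sample size of 40 (2 centres × 2 groups × 10) is taken from an earlier pilot study. The article gives no expected number of late exclusions. The check is therefore a reading of the sections together, followed by an illustration on assumed inputs.

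**Step 1: when a contra-indication can be found, and in whom.**

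| Period | Prehabilitation group | Control group |
|---|---|---|
| Baseline assessment | Walk, steep ramp and strength tests | The same tests |
| Between baseline and the pre-surgery tests | Supervised high-intensity sessions, three days a week | No scheduled physical test or supervised session |
| Week before surgery | Physical tests | The same tests |

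In the first row the rule can act alike in both groups. In the second row only one group is regularly observed under load by a physiotherapist. A control also has no training to stop, so the safety reason has little force there. Unequal detection in this period is an inference from the design; the article does not state it.

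**Step 2: simulated shift with no true effect.** The simulation used 10,000 runs with 20 patients analysed per group. The *k* least fit of 20 + *k* entrants were removed, either from the trained group only or from both groups. Assumptions: *k* = 1 to 4, and a correlation between fitness and outcome of 1.0 or 0.5.

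| *k* removed | Trained group only, correlation 1.0 | Trained group only, correlation 0.5 | Both groups alike |
|---|---|---|---|
| 1 | 0.09 SD | 0.04 SD | about 0 |
| 2 | 0.17 SD | 0.08 SD | about 0 |
| 3 | 0.23 SD | 0.12 SD | about 0 |
| 4 | 0.29 SD | 0.14 SD | about 0 |

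**Step 3: the same idea on clinical scales.** Assume that a fraction *f* of 10% to 20% is removed from the trained group only, with a complication rate of 60% in such patients and 30% in the rest. The intact control group then has a rate of 0.30(1 − *f*) + 0.60*f*:

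- *f* = 0.10: 0.27 + 0.06 = 0.33
- *f* = 0.20: 0.24 + 0.12 = 0.36

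The trained group after removal shows 0.30, so the spurious difference is 3 to 6 percentage points. If the walk-test change in such patients were 50 m worse, the spurious difference would be *f* × 50 m = 5 to 10 m. None of these inputs comes from the article.

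**The case against.** A reader might infer that the trained group loses its frailest patients. The document does not support that. The rule speaks of the subject in either group, the criterion is study-wide, and controls must meet it too. Both groups also perform a steep ramp test to exhaustion at baseline, whereas training starts at 65% of the capacity reached on that test and is eased when perceived exertion is high. The most provocative exposure may thus come at baseline, in both groups. The timing clause can be read as covering what that assessment reveals, before the programme begins. On that reading this is a delayed eligibility check in a non-randomised study, it breaks no randomised comparison, and the excluded patient never trained. All of this stands for baseline findings.

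Participation might also mean the programme only, and a condensed article may leave follow-up after withdrawal to the full protocol. But the article does state a rule, and even on the narrower reading the sentence leaves follow-up and analysis open. Logging assessed patients and counting drop-outs makes the losses visible without supplying their outcomes.

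The illustrated shifts are small for this study. At a 30% rate with 20 per group, the standard error of a difference is √(2 × 0.30 × 0.70 / 20) = 0.145, a 95% half-width of about 28 percentage points. The planned complication measure is an index and not a percentage. Efficacy is only indicative, and selection and confounding from patient preference are acknowledged. This limits the weight of the point. It does not justify adding an avoidable selection after enrolment.

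**Conclusion.** The point holds in a limited form. The rule is open-ended, with no stated follow-up or data retention. For findings of the shared baseline assessment it is late screening without an evident imbalance. For findings made during the programme it may selectively remove less fit patients from the prehabilitation group, which would bias the between-group functional capacity and clinical comparisons in favour of prehabilitation.

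That direction rests on two inferences: that later contra-indications are detected or acted on mainly in the trained group, and that such patients would have had worse outcomes. The size is unknown. The figures above follow from assumed exclusion counts and outcome differences, and the shift is about zero if exclusions fall equally. No figure in the article is contradicted. The point is worth correcting because the remedy is cheap and later analysis cannot repair the loss.

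**What to change.** Restrict complete exclusion to contra-indications identified at the baseline assessment, and apply the same check in both groups. For those found later, separate stopping the programme from leaving the study. Unless consent is withdrawn, the patient then:

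- stays in the group chosen;
- continues the planned questionnaires;
- has surgical and 30-day outcomes taken from the records;
- is included in the between-group comparisons as enrolled.

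When training stops and which physical tests are done remain clinical decisions, on which no view is taken here.

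The cost is a few lines of protocol wording, as the data are already planned. The downside is that some physical tests will be missing for these patients, and the estimate is slightly diluted by patients who did not complete the training.

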**Fig. 1 Fig1:**
[figure not shown]
SPIRIT-derived overview of time points, assessments and recorded variables. 6MWT, 6-min walk test; BIA, bio-impedance electrical analysis; BMI, body mass index; EORTC QLQ-LC13, European Organisation for Research and Treatment of Cancer, quality of life of cancer patients — lung cancer-specific module; EORTC QLQ-C30, European Organisation for Research and Treatment of Cancer, quality of life of cancer patients module; EQ-5D-5L, general health-related quality of life questionnaire; HADS, Hospital Anxiety and Depression Scale; iMCQ, Institute for Medical Technology Assessment (iMTA) Medical Consumption Questionnaire; Indirect 1-RM strength test, indirect 1-repetition maximum; iPCQ, iMTA Productivity Cost Questionnaire; ISI, Insomnia Severity Index; MIP, maximal inspiratory pressure; PG-SGA, Patient-Generated Subjective Global Assessment; SRT, steep ramp test. *All questionnaires will be sent by e-mail

### Assessments

Both groups will be assessed at baseline, the week before surgery, 6 weeks postoperatively and 3 months postoperatively.

#### Physical status

Patients will undergo an assessment by a physiotherapist to determine functional capacity and will be requested to fill in a questionnaire estimating physical condition.

A questionnaire to estimate physical condition (FitMáx^©^) will be used to estimate the maximum oxygen uptake expressed as VO2max. This questionnaire is developed by one of the authors with an expertise in exercise physiology ([name]) and is validated in 700 subjects varying from healthy status to those with pulmonary disease, heart disease or cancer (Meijer et al. 2022). Results pointed out that the questionnaire had a correlation of 0.93 with VO2max determined with the Cardiopulmonary Exercise Test (CPET), the gold standard to determine functional capacity. The questionnaire will be sent to patients by email at baseline, prior to surgery and 6 weeks as well as 3 months postoperatively.

Additionally, the physiotherapist will determine functional capacity using the 6-min walk test (6MWT), steep ramp test (SRT) and indirect one-repetition maximum (1-RM) strength test. Each test will be followed by a break of approximately 10 min. The tests will be completed at baseline, the week before surgery and 6 weeks postoperatively. The walking distance in metres during the 6MWT is determined by counting the number of times a patient walks back and forth on a straight 30-m track during 6 min. Patients will be encouraged and will receive feedback according to a standardised schedule (according to the American Thoracic Society). Patients will be allowed to use any walking device, if necessary (ATS Committee on Proficiency Standards for Clinical Pulmonary Function Laboratories 2002). With the SRT, functional capacity is determined as maximum short exercise capacity (MSEC) on a calibrated bicycle ergometer (Backer et al. 2007; Stuiver et al. 2017). The test starts with 3 min of warming up at 0 W, followed by an increase of resistance by 25 W per 10 s while maintaining 70–80 rpm. The incremental phase continues until exhaustion occurs, defined as < 60 rpm (Meyer et al. 1997). The MSEC is expressed as total Watt achieved until exhaustion. To determine strength, the 1-RM strength test is the golden standard. In this study, the indirect 1-RM strength test, defined as the weight a person can lift at least two and maximum ten times, will be used because the 1-RM can be strenuous and may cause injuries. The 1-RM is calculated using the Brzycki equation: 1-RM = (used weight/(1.0278–0.0278*number of repetitions) (Reynolds et al. 2006).

To monitor the compliance to the out-of-hospital exercises (described in the “interventions” section) in the intervention group and monitor physical activity in the control group, a hip-worn activity monitor (PAM AM 300, Pam Private Company, Oosterbeek, the Netherlands) will be provided to participants in both groups for the duration of the study. Patients will be asked to wear the activity monitor from the baseline assessment until 3 months after surgery, during daytime from getting out of bed until going to bed.

